**Rationale**

The pathological analysis will be compared to pre-,post- PCI and follow-up OCT readings to establish if composition, size and age predicts residual thrombus pre PCI as measured stent result after PCI and primary and primary endpoint at follow-up as measured by OCT. These results will be published in a separate substudy paper.

- 1. **Study goals and objectives**

Study goal is to compare the performance of the Absorb bioresorbable scaffold with a metallic drug eltuting stent in the STEMI patient.

Hypothesis is that a bioresorbable vascular scaffold (BVS) is non-inferior to standard of care, eg. direct stenting with metallic DES, using direct stenting after thrombus aspiration.

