**2.2.6 Primary endpoint**

Coronary Stent Healing Index (cumulated):

1. Uncovered struts: 2% =1 – 5% =2 – 10% =3 - 15% =4 – 20% =5 – 25% =6 – 30% =7 – 35% =8 – 40% =9

2)    Uncovered struts in fornt of side branch on acquired or persistent malapposed struts. 10% =1 – 20% =2 – 30% =3 etc… til 100%=10

3)     Persistent malapposition: ≥2 nabo struts længde mindst 1 mm =1 ; ≥2mm=3 ; ≥3 mm = 3

4)     Acquired malapposition: ≥2 adjacent struts of at least 1 mm length  =2 ; ≥2mm=4 ; ≥3 mm = 6

5)     Neointimal thickness in one frame >200 =1 - >300 =2  - >400 =3 or diameter stenosis >50% =4 - > 75% =5

6)      Cumulated extra stent lumen increase in match cross sectional analysis: (gns. areal mål): ≥0.2mm2 =1 ; ≥0.4 mm2 = 2; ≥0.6mm2=3 ; ≥0.8 mm2 = 4 ;  ≥1.0 mm2=5 ; ≥1.2 mm2 = 6

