**2.2.7 Secondary endpoints**

**2.2.7.1**

OCT endpoints

1. Area stenosis
2. Lumen late loss
3. Crushed stent segments
4. Malapposition of stent struts
5. Minimum expansion of the stents expressed as absolute area and percentage of the closest reference area,
6. Vessel ostial stent area (acute and at FU)
7. Thrombus burden

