**3.0 Data management and statistical analysis**

**3.1 Primary endpoint**

The primary endpoint in the two groups will be analyzed on patient level using paired t-test. A p-value considered indicating significance will be 5%.

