**3.2 Secondary endpoints and other variables**

Differences in categorical variables between the two groups will be analyzed using the chi-square test or Fisher´s exact test. Continuous variables will be analyzed using independent sample t-test and Mann-Whitney U-test, and time to event data will be analyzed using the Kaplan-Meier method and the log-rank test. OCT and angiographic parameters will be evaluated by Spearman correlation analysis. Binary logistic-regression analysis will be performed to identify independent predictors of difference in outcome. Pre and post PCI OCT of vessel size, lesion severity, lesion length. All p-values are two-sided. Level of significance is 5%. The analysis is performed on an intention to treat basis and by actual treatment.

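### Section 3.2 offers only binary logistic regression for finding independent predictors; applied to the Healing Index or a continuous OCT endpoint, it would need an avoidable cut and lose power

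*Protocol*

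**What the plan says.** Section 3.2, on secondary endpoints and other variables, plans the search for predictors in one sentence: "Binary logistic-regression analysis will be performed to identify independent predictors of difference in outcome". It does not say which outcome is meant. A fragment without a verb follows shortly after and appears to list the candidate predictors: "Pre and post PCI OCT of vessel size, lesion severity, lesion length".

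Other parts of the protocol bear on the choice of model:

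- **Primary endpoint (2.2.6).** It is a cumulated score that adds points over six OCT items. No threshold is set for the total. Section 3.3 says the score has not been validated in earlier studies.
- **OCT secondary endpoints (2.2.7.1).** Several are continuous, including area stenosis, late lumen loss and "Minimum expansion of the stents expressed as absolute area and percentage of the closest reference area".
- **Clinical secondary endpoints (2.2.7.3).** Most are yes/no events: death, infarction, stent thrombosis, revascularization.
- **Other analyses.** The score is compared between arms undivided: "The primary endpoint in the two groups will be analyzed on patient level using paired t-test" (whether a paired test is right is a separate matter). Continuous variables get t-tests and Mann-Whitney tests. For association, "OCT and angiographic parameters will be evaluated by Spearman correlation analysis".
- **Thrombus analysis (Rationale).** It aims to "establish if composition, size and age predicts residual thrombus pre PCI", and also to predict the "primary endpoint at follow-up as measured by OCT". It names no model and assigns the results to a separate paper.

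**The concern.** The aim in section 3.2 is to find independent predictors, which calls for a multivariable model. The only one named accepts a two-valued outcome. The trial's main measurements are a multi-point score and continuous OCT quantities, and the listed predictors (vessel size, lesion severity, lesion length on OCT) are natural candidates for explaining OCT results. Spearman correlation keeps the full scale but cannot separate one predictor from another.

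If the logistic model is used on these outcomes, each must be reduced to high or low. Patients on the same side of the cut are then treated as identical, so a real predictor is more likely to be missed. The list of predictors found would also depend on where the cut is placed, and an unvalidated score offers no established place for it.

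**Working it through.** **1. The plan's own figure.** Section 3.3 gives SD 1.39 mm², margin 0.72 mm², alpha 0.05 and power 0.85. With a one-sided 5% test:

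n per group = 2 × SD² × (z₀.₉₅ + z₀.₈₅)² / margin² = 2 × 1.39² × (1.645 + 1.036)² / 0.72² ≈ 53.6, rounded up to 54.

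The stated 54 per group reproduces (power at 54 is 85.2%). It concerns the comparison of arms on minimum flow area. The protocol gives no power for the predictor analysis. Only the total of 2 × 54 = 108 is carried forward, with the planned 120 as a second value.

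**2. Information kept after a cut.** For a roughly normal outcome cut at quantile q, with c the normal deviate at q, relative efficiency is φ(c)² / [q(1 − q)].

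- Median: 0.3989² / 0.25 = 0.637
- 75/25 split: 0.3178² / 0.1875 = 0.539

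**3. Power for one predictor.** The correlation r between predictor and outcome is an assumption, so a range is shown. On the full scale, power ≈ Φ[atanh(r) × √(n − 3) − 1.96]. After a cut, r is replaced by r × √(relative efficiency).

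Example, n = 108 and r = 0.25:

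- Full scale: 0.2554 × √105 = 2.617, and Φ(0.657) = 74.4%.
- Median split: r becomes 0.25 × √0.637 = 0.1995; 0.2022 × √105 = 2.072, and Φ(0.112) = 54.4%.
- Loss: 20.0 points.

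| r (assumed), n = 108 | Full-scale power | After median split | Loss, median (points) | Loss, 75/25 (points) |
|---|---|---|---|---|
| 0.10 | 17.7% | 13.0% | 4.7 | 6.0 |
| 0.15 | 34.1% | 23.4% | 10.7 | 13.6 |
| 0.20 | 54.7% | 37.8% | 16.9 | 21.8 |
| 0.25 | 74.4% | 54.4% | 20.0 | 26.8 |
| 0.27 | 81.0% | 61.2% | 19.8 | 27.1 |
| 0.30 | 88.7% | 70.6% | 18.1 | 25.7 |
| 0.35 | 96.3% | 83.7% | 12.6 | 19.5 |
| 0.40 | 99.1% | 92.3% | 6.8 | 11.9 |
| 0.50 | about 100% | about 99% | 0.9 | 2.4 |

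With n = 120 the median-split losses at r = 0.20, 0.25 and 0.30 are 17.9, 19.9 and 16.6 points.

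**4. Check by simulation.** Linear and logistic regression were fitted to the same simulated data (n = 108, four covariates including arm, 1,500 runs per setting). Median-split losses at r = 0.15, 0.20, 0.27 and 0.35 were 10.9, 18.6, 21.3 and 12.3 points, within 2 points of the table. At 75/25 they were 13.0, 21.9, 28.3 and 20.1.

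**The case against.** The strongest reply is that section 3.2 never says the regression is for the primary endpoint. The primary endpoint has its own section and is compared undivided. Logistic regression is the standard model for the yes/no endpoints in 2.2.7.3, so nothing in the text forces a cut. This stands, and the point is therefore conditional on the outcome chosen.

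A reader might infer more than the documents support in five ways:

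- **That the thrombus question must go through this model.** The Rationale names no model, refers to a separate paper, and uses predictors (composition, size, age) other than those listed in 3.2.
- **That at least 15 points of power are always lost.** For a median split at n = 108, the table shows such a loss only in a middle band. It begins between r = 0.15 and 0.20 and ends between 0.30 and 0.35.
- **That most of the information is thrown away.** A median split keeps about 64% and a 75/25 split about 54%.
- **That the method is unworkable for clinical events.** The protocol gives no event rate. An assumed 5 to 10% would give 120 × 0.05 = 6 to 120 × 0.10 = 12 events, too few for several predictors. That rate is only an assumption, and it was not examined for each binary endpoint.
- **That the unnamed outcome and cut are themselves errors.** A statistical analysis plan could supply both.

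What the reply does not remove is the choice of model family. Section 3.2 names a binary model and no other. A later plan that used a linear or ordinal model for the score would depart from that wording, while one that kept to it would have to cut the score. The planned Spearman correlations lessen the risk of missing an association, but they cannot identify independent predictors.

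**Conclusion.** The point holds in conditional form and is minor. The only multivariable method named fits the binary clinical endpoints but not the Healing Index or the continuous OCT endpoints. For those, a full-scale model is more efficient and needs no threshold.

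For correlations of 0.20 to 0.30 at n = 108, the avoidable loss from a median split is about 17 to 20 points of power. Outside that band it is smaller: about 5 points at 0.10, 7 at 0.40 and 1 at 0.50. A 75/25 cut costs up to about 27 points. These figures assume a roughly normal outcome, a two-sided 5% test, and effect sizes that the protocol does not give. A strongly skewed score would change them.

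The consequence is confined to an exploratory analysis. The between-arm tests use undivided values, and the 54 per group does not depend on this regression.

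**What to change.** In section 3.2, replace the logistic-regression sentence with text along these lines:

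> Predictors of the Coronary Stent Healing Index and of continuous OCT endpoints will be analysed by multivariable linear regression on the full scale, or by proportional-odds regression if the distribution is strongly skewed, with treatment arm in the model. Binary logistic regression will be used only for endpoints that are binary by definition, with the number of predictors limited by the number of events. These analyses are exploratory.

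The logistic part should stay multivariable where events allow, because fitting one predictor at a time could not identify independent predictors.

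The cost is wording only, with no extra patients, measurements or visits. The small downside is that effects are reported in score points or ordinal odds ratios in place of simple odds ratios.

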**3.3 Sample size calculation**

The Coronary Healing Score has not previously been validated in studies. The sample size calculation is therefore done using a Minimum flow Area (MinFA), the endpoint used in the TROFI trial, also investigating STEMI patients with OCT at follow up.

Following the assumptions of a Non-Inferiority design the sample size calculations of this study were based on pooled data of Cardialysis database from multiple trials in acute coronary syndrome where the MinFA was 4.95 + 1.39 mm2. The trial is powered for testing of noninferiority for the primary angiographic endpoint (Minimum Flow Area). In order to be able to reject the null hypothesis that standard treatment with DES produces a MinFA of at least 0.72mm2 better then the experimentaly treated group (BVS) requires a sample size of 54 patients per treatment group (alpha = 0.05 , power = 0.85 , predefined noninferiority margin = 0.72 mm2).

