**2.0 Study design**

The study is a prospective, randomized, controlled, non-blinded, multicenter study comparing metallic drug eluting stent with bioresorbable scaffold in STEMI patients. Primary endpoint Coronary Stent Healing Index, see 2.2.6 for definition.

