**2.2.8 Endpoints definitions: OCT**

Follows definitions from the “Consensus Standards for Acquisition, Measurement, and Reporting of Intravascular Optical Coherence Tomography Studies” paper by Tearney et al. JACC 2012

- - Segments to follow definitions in coming consensus standards
- Quantitative measurements
  - Segments to follow definitions in coming consensus standards
- Primary endpoint is Coronary Healing Score, see 2.2.6 for definition.

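### Section 3.3 sizes the trial on Minimum Flow Area and calls it primary, but the declared primary is the healing index, and no endpoint list or analysis section names the powered test

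*Protocol*

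**What the plan says.** Three places name the healing index as the primary endpoint:

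- Section 2.0: "Primary endpoint Coronary Stent Healing Index, see 2.2.6 for definition".
- Section 2.2.6, under the primary endpoint heading: "Coronary Stent Healing Index (cumulated", followed by six scored components. MinFA is not one of them.
- Section 2.2.8: "Primary endpoint is Coronary Healing Score, see 2.2.6 for definition".

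Section 3.3 first explains why the sample size does not use that endpoint: "The Coronary Healing Score has not previously been validated in studies". It goes on: "The sample size calculation is therefore done using a Minimum flow Area (MinFA), the endpoint used in the TROFI trial". It then gives a null hypothesis, a direction, a margin of 0.72 mm², alpha 0.05 and power 0.85, all for MinFA, and labels that variable: "The trial is powered for testing of noninferiority for the primary angiographic endpoint (Minimum Flow Area".

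Section 6 states the expected result as no difference in minimal flow area, and mentions secondary endpoints separately. It does not mention the index.

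Section 3.1 tests the primary endpoint with a t-test at 5% and gives no margin. Section 3.2 covers secondary endpoints and other variables with difference tests, and says p-values are two-sided at 5%. Section 3.4 names the analysis populations.

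**The concern.** The hypothesis in the study goals is non-inferiority. A non-inferiority conclusion needs one endpoint that has a margin, a sample size and a planned test. Here these are split. The endpoint with a margin and power appears in no endpoint list, and no analysis section names its test. The endpoint that is listed as primary and tested in 3.1 has no margin, no standard deviation and no power.

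Two things are at stake. First, the analysis sections as written would not carry out the comparison for which 120 patients are recruited. Second, because 3.3 and section 6 treat MinFA as primary, it is unclear which result answers the main question. That matters more in an open trial whose core laboratory, by section 4.2, is not blinded to arm, since a single primary endpoint fixed in advance is one of the main safeguards left.

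**Working it through.** **Inputs**

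- Section 3.3: "where the MinFA was 4.95 + 1.39 mm2". The plus sign is read as plus/minus, so SD = 1.39 mm².
- Section 3.3: margin 0.72 mm², power 0.85, alpha 0.05 (one- or two-sided not stated), 54 per group.
- Sections 2.2 and 2.3: 120 patients randomized 1:1, so 60 per arm.
- Assumed: true difference of zero, equal SD in both arms, normal approximation.

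**Reproducing the plan's figure**

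n per arm = 2 × SD² × (z for alpha + z for power)² / margin²

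- One-sided 5%: 2 × 1.39² × (1.645 + 1.036)² / 0.72² = 53.6, rounded up to 54. This matches. A noncentral t calculation gives 55, an immaterial difference.
- One-sided 2.5%: 2 × 1.39² × (1.960 + 1.036)² / 0.72² = 66.9, rounded up to 67. This does not match.

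The 54 therefore comes entirely from MinFA and holds only at one-sided 5%.

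**Power for MinFA**

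Power = Φ(margin / (SD × √(2/n)) − z for alpha)

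| n per arm | one-sided 5% | one-sided 2.5% |
|---|---|---|
| 54 | 85.2% | 76.8% |
| 60 | 88.3% | 81.0% |

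For example, at n = 60: 0.72 / (1.39 × √(2/60)) = 2.837. Then Φ(2.837 − 1.645) = 88.3% and Φ(2.837 − 1.960) = 81.0%.

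**Power for the index**

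This cannot be computed, because the protocol gives neither an SD nor a margin for it. For illustration only, assume a non-inferiority margin expressed in SD units of the index, 54 per arm, one-sided 5% and a true difference of zero:

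| assumed margin (SD) | power |
|---|---|
| 0.3 | 47% |
| 0.4 | 67% |
| 0.5 | 83% |
| 0.6 | 93% |

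Power of 85% would need a margin of about 0.52 SD, which is the ratio that MinFA happens to have (0.72 / 1.39 = 0.518). Nothing in the protocol supports that ratio for the index.

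**Where MinFA appears**

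- Section 2.2.6 (index components): absent.
- Section 2.2.7.1 (OCT): absent. Related items are area stenosis, lumen late loss and "Minimum expansion of the stents expressed as absolute area and percentage of the closest reference area". None of them is a minimum flow area, so the 0.72 mm² margin on flow area applies to none of them.
- Section 2.2.7.2 (angiographic): absent, so reading 3.3 as meaning primary within the angiographic class does not rescue the label.
- Section 2.2.7.3 (clinical): absent.
- Sections 3.1, 3.2 and 3.4: no MinFA test and no use of 0.72 mm².
- Sections 3.3 and 6: present.

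**The case against.** The strongest defence is that sizing on a related measure is a recognised choice when the chosen endpoint has no usable SD, and that section 3.3 does this openly and gives its reason. That stands. It justifies MinFA as the basis for sizing. It does not justify calling MinFA primary, and it does not give the index any power.

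Four stronger readings are tempting, and the document does not support them:

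- *That the plan claims 85% power for the index.* It does not. Section 3.3 ties the 85% and the margin to MinFA.
- *That MinFA will never be analysed.* Section 3.3 states a null hypothesis for it, and the general rule in 3.2 for continuous variables could produce a two-sided difference test. A separate statistical analysis plan, not available here, might hold more. What can be said is that no endpoint list or analysis section of the protocol names the non-inferiority test that was powered.
- *That there are two equally declared primaries, or an intention to choose between them later.* Three sections name the index consistently, and 3.3 opens by treating MinFA as a stand-in. The label in 3.3 and the wording of section 6 create ambiguity. They say nothing about intent.
- *That MinFA must therefore become the primary.* That would change the trial's question. It is open to the sponsor but is not a required correction.

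Leaving the matter to an analysis plan is not a sufficient answer: which endpoint is primary is a protocol decision, and the protocol contradicts itself on it.

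**Conclusion.** The plan is wrong as written. Section 3.3 gives MinFA a primary label that contradicts 2.0, 2.2.6 and 2.2.8, and the powered non-inferiority comparison is missing from the endpoint lists and from sections 3.1, 3.2 and 3.4.

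In size: 85.2% power at 54 per arm is correct for MinFA at one-sided 5%, with SD 1.39 mm² and no true difference. If the two-sided 5% in 3.2 is carried over as one-sided 2.5%, the same 54 gives 76.8%, and the planned 60 gives 81.0% if nobody is lost. For the healing index no power can be derived at all.

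The contradiction and the missing listing rest on the text alone. The power figures rest on the SD and margin in 3.3 and the normal approximation.

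**What to change.** Keep the healing index as primary and amend as follows:

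1. **Section 2.2.7.1:** add MinFA by OCT at 12 months as the key secondary endpoint.
2. **Section 3:** add its non-inferiority test. BVS is non-inferior if the upper confidence bound for mean MinFA, DES minus BVS, lies below 0.72 mm².
3. **Alpha:** state it for that test. One-sided 5% (upper limit of a two-sided 90% interval) agrees with 54 per arm but must be reconciled with the two-sided 5% in 3.2. One-sided 2.5% needs 67 per arm, above the planned 60, so the power statement would then have to be lowered or the number raised.
4. **Section 3.3:** relabel MinFA as the key secondary OCT endpoint. State that the 85% applies to MinFA only and that no power is established for the index.
5. **Section 6:** reword so that MinFA is no longer set apart from the secondary endpoints as if it were the primary.

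The cost is amendment text, plus a MinFA reading by the core laboratory from OCT runs already planned under 2.6. The protocol does not say that this variable is read now. The healing-index result will carry no power claim. If the sponsor prefers MinFA as primary, sections 2.0, 2.2.6, 2.2.8 and 3.1 must change together, and the alpha question in step 3 must be settled first.

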**2.3 Treatment step-by-step**

Before arrival et cath lab, loading with acetylic salisylic acid and one of the antiplatelet agents clopigrogel/pragusgrel/ticagrelor is mandatory. Heparin or bivalirudin at start of procedure. After angiography and confirmation of presence of thrombus GpIIb/IIIa inhibitors are administered at operators discretion.

After thrombus aspiration with TIMI flow 2 or more the patient will be asked to participate in the study. Oral consent witnessed by staff non-affiliated with the study will be obtained.

OCT scan will be performed after 0.2 mg intracoronary nitroglycerine for sizing and lesion evaluation. The patient is then randomized into one of two arms in a 1:1 distribution:

1. Direct stenting with everolimus eluting stent
2. Direct stenting with bioresorbable stent

Direct stenting is the preferred method of implantation to keep procedure as short and simple as possible. Predilatation will not considered protocol violation if deemed necessary by operator. After stenting and post dilation at operator’s discretion, a second OCT will be performed. Any further post dilatation will be performed at operator’s discretion. A final OCT will be done if further postdilatation is performed. 0.2 mg intracoronary nitroglycerine is administered before each OCT scan.

Patient will be asked to sign an informed consent after the procedure (<24 hrs).

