**6 Expected outcome of the study**

We expect to find no difference in the minimal flow area, or the secondary endpoints of MACE and stent failure.

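### The 85% power at 54 per group holds only at a one-sided alpha of 5%, which the protocol never states; at two-sided 5%, the only sidedness it declares, power is about 76%

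*Protocol*

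**What the plan says.** Three places in section 3 of the protocol bear on the error rate.

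- Section 3.3 bases the sample size on MinFA. It takes its variability from pooled data ("MinFA was 4.95 + 1.39 mm2", where the plus sign is read as plus/minus), frames a null hypothesis in which the metallic stent is better by at least the margin, and arrives at "54 patients per treatment group (alpha = 0.05 , power = 0.85 , predefined noninferiority margin = 0.72 mm2". The alpha has no sidedness attached.
- Section 3.1, on the primary endpoint, says: "A p-value considered indicating significance will be 5" per cent. It gives no sidedness either.
- Section 3.2, headed as covering secondary endpoints and other variables, says: "All p-values are two-sided. Level of significance is 5" per cent.

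No section mentions a one-sided test, or a 90% or 95% confidence interval for the non-inferiority decision. Section 2.2 plans 120 patients and section 2.3 allocates them 1:1, so 60 per group. No dropout rate is given.

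**The concern.** A power figure means something only together with the error rate at which the test will be run. The one explicit statement on sidedness is two-sided 5%. By the usual convention, a non-inferiority claim consistent with that uses the 95% confidence interval, which is a one-sided 2.5% test. If 54 per group was derived at one-sided 5%, the plan quotes power for a more lenient test than the one that section 3.2 points to.

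Two things are at stake. Under the two-sided rule, the trial has less chance of showing non-inferiority than it states. Under the one-sided 5% rule, the risk of accepting a scaffold whose MinFA is worse by the full margin is 5%, twice the 2.5% that a 95% interval allows. With the choice left open, two analysts could apply different intervals to the same data and disagree on non-inferiority.

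**Working it through.** **Inputs.** SD 1.39 mm2, margin 0.72 mm2, power 0.85, 54 per group (all section 3.3). Allocation 1:1 (section 2.3). Enrolment 120, so at most 60 evaluable per group (section 2.2). True difference 0: section 3.3 gives no value, but section 6 says "We expect to find no difference in the minimal flow area".

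**Formula (normal approximation).** n per group = 2 × SD² × (z for alpha + z for power)² / margin².

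The common factor is 2 × 1.39² / 0.72² = 3.8642 / 0.5184 = 7.454.

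**Step 1: reproduce the plan's figure.** One-sided alpha 0.05: (1.645 + 1.036)² × 7.454 = 53.6, so 54. This matches section 3.3. The exact noncentral t calculation gives 55, a trivial difference.

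**Step 2: the same design at two-sided 5% (one-sided 2.5%).** (1.960 + 1.036)² × 7.454 = 66.9, so 67 per group (134 in total). The noncentral t gives 68 (136 in total). Both totals exceed 120. A two-sided equivalence version gives 71 per group, so it does not explain the 54 either.

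**Step 3: power at the planned sizes.** The standard error of the difference is 1.39 × √(2/n).

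- n = 54: standard error 0.2675, and 0.72 / 0.2675 = 2.69.
- n = 60: standard error 0.2538, and 0.72 / 0.2538 = 2.84.

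Power is the normal probability below that ratio minus z for alpha.

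| Evaluable per group | One-sided 5%: normal / noncentral t | One-sided 2.5%: normal / noncentral t |
|---|---|---|
| 54 | 85.2% / 84.8% | 76.8% / 76.0% |
| 60 | 88.3% / 88.0% | 81.0% / 80.3% |

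**Step 4: what the ambiguity does to a decision.** With 54 per group and the observed SD equal to 1.39, non-inferiority is claimed if the observed MinFA deficit of the scaffold is below:

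- 90% interval: 0.72 − 1.645 × 0.2675 = 0.28 mm2
- 95% interval: 0.72 − 1.960 × 0.2675 = 0.20 mm2

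An observed deficit between about 0.20 and 0.28 mm2 is therefore a success under one rule and a failure under the other.

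**The case against.** The strongest defence is that section 3.3 is coherent on its own terms. Its null is directional, a directional null is tested in one direction, and a one-sided 5% test gives exactly 54. The two-sided sentence sits under a heading for secondary endpoints, after a list of tests for differences and associations, so it need not govern the non-inferiority test. Reading two-sided 5% as a 95% interval is also a convention that the protocol does not spell out.

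Much of this stands. A reader might infer that all the analysis sections prescribe two-sided testing and that 3.3 flatly contradicts them. The documents do not support that: only 3.2 says two-sided, and 3.1 is silent. A reader might also infer that 54 is an arithmetic mistake. It is not; it follows from the stated inputs at one-sided 5%. Nor is one-sided 5% ruled out as a choice for non-inferiority.

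What the defence does not remove is that the protocol never writes one-sided for this test. Section 3.2 speaks of all p-values and is the only sidedness rule there is. If it is held not to apply, the powered test has no declared sidedness and the same correction is needed.

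A second defence is that 120 patients are planned, not 108. That raises power under the two-sided rule to 80–81%, still below 85%, and only if nobody is lost. Sections 11.3 and 11.4 allow for patients who decline the follow-up angiography or do not return.

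**Conclusion.** The point holds as an inconsistency of sidedness, not as a miscalculated sample size. The stated 85% belongs to a one-sided 5% test. Under the only sidedness that the protocol declares, the design has 76–77% power at 54 evaluable per group and 80–81% at 60, and 85% would need 67–68 per group. At 54 per group the type II error is then about 23–24% rather than 15%.

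These figures assume a true difference of zero, an SD of 1.39 mm2, and that two-sided 5% translates into a 95% interval for non-inferiority.

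It would be tempting to conclude that the trial is underpowered for its primary endpoint. The documents do not support that from this calculation. The primary endpoint in section 2.2.6 is the Coronary Stent Healing Index, while section 3.3 calculates on MinFA because the index had not been validated. The shortfall described here is in the MinFA power statement only, and correcting it supplies neither a margin nor a power figure for the index.

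**What to change.** In section 3.3, state the sidedness and the power that goes with it, choosing one of two forms:

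1. One-sided alpha 0.05, judged by a two-sided 90% confidence interval, power 85% at 54 evaluable per group; and in section 3.2 exempt this test from the two-sided rule.
2. One-sided alpha 0.025, judged by a two-sided 95% confidence interval, power about 76% at 54 and about 80% at 60 evaluable per group.

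Either form should be fixed before outcome data are seen. Neither needs more patients or procedures. The first costs an openly stated 5% one-sided error rate, which readers may find lenient. The second costs a less favourable power figure. Keeping 85% power under the second form would instead need 67–68 evaluable patients per group, which is more than the planned enrolment.
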